## Abstract

**Introduction:**

Chronic osteomyelitis is a serious osteoarticular infection that most often occurs in the long bones, responsible for significant morbidity with the risk of fracture and amputation. Despite advances in both antibiotics and surgical treatment, the probability of recurrence of infection remains at around 20%. Cerament-G (BONESUPPORT AB, Sweden) is a synthetic bone substitute that fills the bone void left by surgery, prevents infection and promotes bone regeneration within this space. Cerament-G also provides the local delivery of high doses of gentamicin over several weeks. Two prospective observational studies described a number of infectious recurrences of 4 and 5% after the use of Cerament-G. Although available in France, Cerament-G is currently not reimbursed and its high cost constitutes a barrier to its use. We hypothesize that the use of Cerament-G will lead to fewer costs to the collectivity while improving patient utility and, as an innovative strategy, will be superior to standard of care on recurrence of infection.

**Methods and analysis:**

The Conviction Study is a prospective, multicenter, randomized, single blind study conducted in 14 French Reference Centers for Complex Osteoarticular infections. The main objective is to evaluate the cost-effectiveness of using Cerament-G in the treatment of chronic long bone osteomyelitis by comparing this innovative strategy to standard of care. A cost-utility analysis from the collective perspective will be conducted over a 24-month time horizon after the initial surgery. The outcome for the main medico-economic evaluation will be Quality Adjusted Life Years (QALYs).

**Discussion:**

The study is being conducted throughout the CRIOAc network in France, in referral centers for the management of complex infections which will facilitate patient recruitment. This study has several limitations: the investigators have to be trained to handle the device, and it was impossible to blind the surgeon.

**Conclusion:**

If the use of Cerament-G is demonstrated to be superior to leaving the dead space empty during surgery for patients with stage III chronic long bone osteomyelitis, its use will be recommended to improve the prognosis of such patients, and this device may eventually qualify for reimbursement through the French Health Insurance scheme.

**Ethics and dissemination:**

This protocol received authorization from the Ethics Committee CPP Sud Méditerranée V on April 27, 2021 (21.03.10.77652) and the French National Agency for Medicines and Health Products on May 6, 2021 (2020-A02299-30). Results will be disseminated to the scientific community through congresses and publication in peer-reviewed journals.

## Introduction

1.

### Rationale

1.1.

Chronic osteomyelitis (stage III of the Cierny-Mader classification) is a serious osteoarticular infection which most often occurs in the long bones (tibia, femur, humerus, forearm), responsible for significant morbidity with risk of fracture and amputation. It is due to the presence of bacteria in the bone marrow, sometimes responsible for an intraosseous abscess, also called brodie abscess (1).

Chronic osteomyelitis can have a hematogenous or more often exogenous origin, after trauma or surgery. The bacteria involved have the ability to modify their metabolism and bring into play persistence mechanisms (such as biofilm) making their eradication difficult. The treatment of chronic osteomyelitis of long bones requires surgery, corticotomy: opening of the cortical bone to perform endomedular curettage to identify the bacteria, remove any sequestra (bone fragments to which the bacteria adhere in the form of biofilm), and reduce bacterial inoculum. Indeed, debridement of the intramedullary canal is essential to remove sequestrum where the bacteria is embedded in biofilm, to cure the disease. Access to the endomedular space involves the cutting of an elongated rectangular window parallel to the axis of the bone. This is the best approach structurally. The window should be no larger than 7 to 10 mm in diameter and 3 to 9 cm in length, depending on the size of the bone. If the size has to be bigger, the surgeon has to evaluate the risk of iatrogenic fracture and the potential need for preventive stabilization (usually not needed when ≥70% of the original cortex remains intact). Patients at particularly high risk of fracture (15% to 25%) may also need preventive stabilization during surgery (osteosynthesis or external fixator). The management of the “dead space” produced by endomedular debridement is still debated. In order to avoid the occurrence of post-debridement endomedular hematoma, some authors have discussed several possibilities. Some suggest autologous bone graft. Some prefer the use of antibiotic-impregnated PMMA cement; beads or cementoplasty that fill the entire bone void, but this strategy would require a new surgical intervention to remove the cement. There is also the Papineau technique involving serial open bone grafting. Lastly, there is the possibility of skin graft, whereas bone grafting is not biomechanically useful in stage III osteomyelitis. None of these techniques are considered as the standard of care procedure for bone void management, practices seem to be largely heterogeneous, and leaving the dead space empty, is clearly also an option to limit complications induced by iterative interventions. Indeed, a two-stage approach, with use of a PMMA cement to prepare the performance of a bone graft during the second stage, has to be considered during stage IV osteomyelitis (septic non-union), but not in stage III osteomyelitis. The two-stage approach would help to obtain an induced membrane that facilitates the bone grafting, and then obtain the consolidation of the disrupted long bone, i.e., to restore the continuity and the union of the long bone. Indeed, there is no biomechanical need for bone grafting in stage III osteomyelitis of long bone. However, in stage III as in stage IV osteomyelitis, a surgical act of “skin and soft tissue cover” called “flap” can be necessary, in particular in patients presenting an old attack with weakening and adhesion of the skin and soft tissues to the underlying bone. The flap could be done during the same time as the bone debridement, or could be done during a second operative procedure (2, 3).

Post-operatively, the patient receives a probabilistic systemic antibiotic therapy then a systemic antibiotic therapy targeted on the identified germ, for a period of 3 months. The effectiveness of these antibiotics relies on their ability to penetrate bone tissue. Despite the progress made in both antibiotics and surgical treatment, the probability of failure of this treatment (infectious recurrence) is around 20%, and has unfortunately remained stable for more than 20 years (1, 4). A single-center study published in 2018 (4) followed 116 patients for at least 1 year after discharge from hospital for treatment of osteomyelitis of the long bones of the lower and upper limbs (the class was not specified). In total, 26 infectious recurrences (22.4%) were observed with an average delay of 11.2 months (95% CI = 3.3–19.1). Recurrences could be explained by the persistence of the initial germ despite a well-conducted treatment or by superinfections with other bacteria, acquired during surgery, which took advantage of the “dead space” generated by the surgical curettage. In the event of failure, a new surgical and antibiotic sequence is often proposed, with a new risk of fracture or even amputation (approximately 5% of patients experienced treatment failure) due to bone weakening and iterative surgeries.

Local antibiotic therapy could be a solution, but so far, it has not been clearly considered and recommended due to the lack of a “carrier” or a device that could stabilize and release an antibiotic locally over several weeks.

Some bone substitutes have been developed in this indication, such as Osteoset-T (WRIGHT MEDICAL FRANCE, France), a synthetic bone substitute composed of calcium sulfate and supplemented with tobramycin, CE marked and marketed in Europe in 1998. It was approved by the French National Health Authority for bone filling on an infected site in cases of osteitis on continuous bone (5). A 2018 report by the Health Technology and Intervention Evaluation Unit of the University Hospital Centre of Québec, on the use of calcium sulfate impregnated with antibiotics for the prevention and treatment of infections, concluded that: “the available data suggest a possible beneficial effect of calcium sulfate impregnated with antibiotics in the treatment of infections and more particularly of osteomyelitis.” However, the literature review carried out showed great heterogeneity in the studies and practices used for the management of these patients, in the types of substitutes (components, types and doses of antibiotics), and in the definition of recurrence and follow-up periods. The publications selected studied Osteoset-T or Stimulan (calcium sulfate beads impregnated extemporaneously with an antibiotic), and reported an infection eradication rate of between 80 and 92% in comparative studies, with a minimum follow-up of less than 1 year post-surgery. The only randomized study (6) compared polymethyl methacrylate cement beads (non-absorbable) impregnated with an antibiotic with Osteoset-T. A total of 14 patients were included in each group, and 2 patients had an infectious recurrence in each group (14%; mean follow-up 38 months). In terms of tolerance, the main risks of adverse effects found in the literature, with a low occurrence rate, were related to calcium sulfate (hypercalcemia, inflammatory reactions with exudates around wounds of a serious nature, heterotopic ossification, and allergy) or depended on the type of antibiotic used, including a risk of transient acute renal failure. These data are of real interest for the management of a disease such as chronic osteomyelitis; unfortunately, Osteoset-T has not been available on the French market since 2010.

A new synthetic bone substitute composed of hydroxyapatite, calcium sulphate, and gentamicin, Cerament-G (BONESUPPORT AB Laboratory, Sweden), has been developed and was CE marked in 2013. This substitute fills the “dead space” that is formed during surgery, prevents this cavity filled with blood from becoming infected, and promotes the regeneration of the bone within this space, limiting the risk of fracture to medium and long term. The device comes as a powder to be reconstituted in a pre-filled syringe and takes the form of a paste that hardens over time. There is a precise timing to be observed, between the time of mixing, the application, and skin closure. Cerament-G also delivers locally for several weeks very high doses of gentamicin (concentration of 17.5 mg/ml in the device), a broad-spectrum bactericidal antibiotic effective against the vast majority of bacteria involved in osteoarticular infections. It provides effective local antibiotic therapy through broad local exposure to this antibiotic, at prolonged concentrations for several weeks. Initially around 1,000 mg/l, the local concentrations, thus obtained, then remain well above the minimum inhibitory concentration of the bacteria potentially involved, with local release of gentamicin for more than 21 days (7). Low plasma concentrations of gentamicin have been noted (8, 9) showing a low passage of the antibiotic systemically.

The combination of local and systemic antibiotic therapy is expected to provide a benefit in terms of anti-infective activity. The high local concentrations of gentamycin diffused in the hours and days following insertion by the device are complementary to systemic antibiotic therapy, which uses molecules whose bone penetration is variable. There is a real theoretical complementarity in terms of pharmacokinetics between local antibiotic therapy and systemic antibiotic therapy. The composition of Cerament-G (hydroxyapatite and calcium sulphate) also promotes bone regeneration and could therefore limit the risk of fracture following corticotomy.

A prospective study was conducted on 100 patients with chronic class III (*n* = 78) or IV (*n* = 22) osteomyelitis (105 bones) (10). The treatment was performed by one-step debridement surgery with the addition of Cerament-G, between March 2013 and February 2015, with a postoperative follow-up of 12 to 34 months (19.5 months on average). An infectious recurrence was observed in 4 patients between 145 days (approximately 5 months) and 563 days (approximately 18 months), all class III (i.e., 5%, 4/78). Recurrence was defined by a positive culture following a biopsy or an aspiration guided by radiology. Eleven patients presented with a minor extraosseous leakage of Cerament-G, visible on radiology, without consequences for the patients. In 6 cases, white wound drainage fluid, with the appearance of liquefied calcium sulphate residues, was observed.

A second prospective non-randomized monocentric study compared 3 antibiotic-impregnated bone substitutes as an adjunct to surgery for the treatment of patients with class III or IV chronic osteomyelitis (11): Septocoll-E (*n* = 74, mean follow-up 1.75 years); Osteoset-T (*n* = 166, mean follow-up 1.96 years); and Cerament-G (*n* = 73, mean follow-up 1.78 years—including 64 class III patients). The infectious recurrence rate for the group treated with Cerament-G was 4.1% (3 patients). In this group, the fracture rate was 1.4% and the leak rate 9.6%. These results were lower than those observed in the other groups (notably twice as low as in the Osteoset-T group; statistically significant differences), despite a percentage of patients presenting a higher risk of recurrence.

Cerament-G is a potential breakthrough innovation in the management of chronic osteomyelitis, but its use is limited in France due to its high cost (up to about €4,000 per procedure depending on the dose), which is not covered by the national health insurance.

However, its use as an adjuvant in the treatment of chronic osteomyelitis of the long bones is expected to avoid resource consumption such as the cost of managing failures (repeated surgeries, prolonged hospitalizations, new intravenous and then prolonged oral antibiotic therapies with sometimes expensive molecules, stays in follow-up care and rehabilitation, etc.) and the cost of managing possible fractures or amputations. The cost of a hospital stay for the treatment of an osteoarticular infection is high since it is estimated by the French national cost study at between €5,518 and €19,608 depending on the level of severity. Similarly, the cost of a hospital stay is estimated between €5,130€ and €18,481 for the amputation of a leg and between €1,875 and €8,892 for a leg fracture depending on the level of severity. At the same time, it will lead to an improvement in the quality of life of patients, in particular because it will make it possible to avoid painful and sometimes ineffective repeated surgeries that can lead to fractures or even amputations. In diabetic patients, Clarke et al. (12) estimated the decrease in utility associated with a limb amputation at −0.280 in the short term. The impact on the utility of a leg amputation is less important in the long term but would always be between −0.039 and −0.173 (13) depending on the treatment. Similarly, the disutility linked to a femur fracture has been estimated at −0.258 in the short term and between −0.058 and −0.402 in the long term depending on the management (13).

The French multicenter CONVICTION study has been developed based on these assumptions, to assess the efficiency of the use of Cerament-G as an adjuvant in the treatment of chronic osteomyelitis of the long bones.

### Objective and hypothesis

1.2.

The main objective is to evaluate the cost-effectiveness of the use of Cerament-G in the treatment of chronic osteomyelitis of long bones. Two strategies will be compared: medico-surgical usual care based on corticotomy (± skin and soft-tissue/muscle flap) followed by systemic antibiotic therapy (standard of care); and medico-surgical care with corticotomy during which Cerament-G is used, followed by systemic antibiotic therapy (innovative strategy).

We hypothesize that, despite the initial additional cost associated with Cerament-G, its use will lead to fewer future costs while improving patient utility. We also hypothesize that the innovative strategy is superior to the standard of care in terms of recurrence of infection.

This study will focus on adult patients with chronic osteomyelitis of long bones, requiring surgical management in one of the referral centers for the management of complex osteoarticular infections in France (“Centre de Référence des Infections Ostéo-Articulaires complexes” [CRIOAc]).

## Methods and analysis

2.

### General information

2.1.

The trial has been registered at the Clinical Trials Registry as NCT04805164.

The CONVICTION Study is a prospective, multicenter, randomized, single blind study comparing two treatment strategies for chronic osteomyelitis of long bones with and without the use of Cerament-G.

Patients will be recruited as part of management care of their chronic osteomyelitis in a CRIOAc, and will be enrolled by the investigator after evaluation in a multidisciplinary consultation meeting.

The participating centers are orthopedic surgery and infectious disease departments from 12 French University Hospital Centers. Study sites can be obtained from the Sponsor’s representative.

Four committees were created as part of this study: a Scientific Committee; a Patient Eligibility Validation Committee; a Clinical Event Validation Committee; and an Independent Safety Committee.

The role of the Scientific Committee is to ensure that the study runs smoothly. The Scientific Committee also participated in the drafting of the protocol. The committee will be regularly informed of the progress of the study by the coordination and, if necessary, will be called upon to make decisions on the study protocol.

The members of the Patient Eligibility Validation Committee will ensure that each patient has a relevant indication for Cerament-G, based on clinical and radiological data. They will propose direct closure without tension or a cover flap following the initial surgery, and the addition of a possible preventive stabilization in case of high risk of fracture (internal fixation or external fixator). Finally, they will specify the volume of Cerament-G to be injected.

The Clinical Event Validation Committee will be composed of three members independent from participating centers, with the task of reviewing available data from each case to comment on the nature of the clinical events (healing, remodeling/consolidation and recurrence of infection) measured by the investigators. The members of this committee will be blinded to patient treatment.

The Independent Safety Committee will only meet if more than three recurrences of infection are observed in the innovative strategy group during the first year of the study. Its members will have to give an opinion on whether or not to continue the study, based on all relevant data, including the conclusions of the Clinical Event Validation Committee.

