#### Participant timeline

2.4.2.

The first inclusion took place on October 14, 2021. Total inclusion period is expected to be 3 years and the duration of participation of each patient will be 25 months. Schedule for enrolment, interventions and assessments are summarized in Table 1.

**Table 1 tab1:** Schedule for enrolment, interventions and assessments.

Moment actions	STEPS							
	V1 Inclusion	V2 Hospitalization / Corticotomy	V3 Follow-up consultation	V4 Follow-up consultation	V5 Follow-up consultation	V6 Follow-up consultation	V7 Follow-up consultation	V8 End of study
	D-60 à D-2	D0	W + 4/W + 6	M3 +/− 15 d	M6 +/− 15 d	M12 +/− 15 d	M18 +/− 30 d	M24 +/− 30 d
Informed consent	X							
Randomization	X							
Antecedents	X							
Urine pregnancy test (only for women of childbearing age)	X							
Physical examination	X		X	X	X	X	X	X
Determination of calcium, phosphorus, albumin, urea, and creatinine (serum creatinine and creatinine clearance / measurement of GFR)	X	X	X	X				
EQ-5D-5L^a^	X		X	X	X	X	X	X
Resource consumption			X	X	X	X	X	X
Professional and informal help	X		X	X	X	X	X	X
Micro-costing^b^		X						
Corticotomy / fracture complication		X	X	X	X	X	X	X
Acute renal failure		X	X	X				
Healing and bone remodeling / consolidation (standard radiology)	X					X		
Infectious recurrence		X	X	X	X	X	X	X
Surgical revision^c^			X	X	X	X	X	X
Amputation			X	X	X	X	X	X
Adverse events	X	X	X	X	X	X	X	X

a In the event of surgical revision, an EQ-5D will be completed by the patient closest to the event.

b Micro-costing will only be carried out for patients included in the innovative strategy, with the use of Cerament-G.

c In the event of surgical revision, the schedule begins again in accordance with post-surgical follow-up, until the normal end of the study, i.e., 24 months after the first corticotomy, is reached.

Patients with chronic osteomyelitis of the long bones (stage III of the Cierny-Mader classification) will be identified during the multidisciplinary meeting carried out within the participating CRIOAc.

The patient, if eligible, is informed of the completion of the study during a visit carried out with a view to planning his surgical intervention (pre-surgical visit) or during a dedicated visit, by the investigator. A written information leaflet is given to the patient.

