#### Sample size calculation

2.10.1.

The sample size calculation has been based on the most relevant clinical efficacy outcome measure, which is the proportion of patients with at least one recurrence of infection at 24 months.

Available data show rates of 4 to 5% when using Cerament-G, for durations between 5 and 21 months (10, 11); as the follow-up is longer in the CONVICTION study (24 months), the hypothesis chosen was a rate of 6%. On the other hand, the proportion of recurrence of infection in the standard of care is estimated at 20% (21). The total number of patients to be randomized in the study will be 200 (100 per group; considering alpha-risk at 0.05, power of 80% in a bilateral situation and approximately 10% of early withdrawal).

The estimate of the number of subjects needed according to medico-economic hypothesis would require numerous hypothesis, leading to uncertainty. Only the cost of Cerament-G and hospitalizations for recurrence of infection, and the impact on the short-term utility of the surgery for recurrence of infection (6% in the innovative strategy vs. 20% in the standard of care), fractures and amputations (5% in both groups) have been taken into account. We hypothesize that the utility is decreased 6 months before revision surgery, 3 months after revision surgery, 9 months after amputation and 3 months after fracture. As no utility data are available in the literature for “before surgery” and “after surgery” conditions, they have been estimated according to expert opinion. As little data is available in the literature for health states comparable to the health states “after fracture” and “after amputation” and for the sake of homogeneity of the measurement, the utility concerning these states has also been estimated by expert opinion. However, these data seem consistent with the closest data available (22).

The utility scores used to value these health conditions are as follows:

- Before surgery = 0.8- After surgery = 0.49- After fracture = 0.28- After amputation = 0.39

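### The Independent Safety Committee's only trigger sits in study year 1: at best about an even chance of firing if device-arm recurrence is twice the standard-of-care rate, and no force after month 12

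*Protocol article*

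**What the plan says.** Section 2.1 (General information) creates four committees. For the Independent Safety Committee the rule is that it "will only meet if more than three recurrences of infection are observed in the innovative strategy group during the first year of the study". Once convened, "Its members will have to give an opinion on whether or not to continue the study, based on all relevant data". The article describes no other independent review of whether the trial should continue.

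The design around this rule is as follows:

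- **Accrual** (2.4.2 Participant timeline): "Total inclusion period is expected to be 3 years". Surgery follows inclusion by up to 2 months, and each patient is followed for 24 months after the first operation.
- **Size** (2.10.1 Sample size calculation): "The total number of patients to be randomized in the study will be 200 (100 per group").
- **Planned 24-month recurrence** (2.10.1): for the device, "the hypothesis chosen was a rate of 6"%; for the control arm, "the proportion of recurrence of infection in the standard of care is estimated at 20"%.
- **Timing in the cited studies** (1.1 Rationale): in the 100-patient device series, the four recurrences fell "between 145 days (approximately 5 months) and 563 days (approximately 18 months"). In the 116-patient single-centre cohort, the mean delay to recurrence was 11.2 months.

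**The concern.** The rule fixes one arm, one event type, a raw count and one calendar window. The window covers the stretch of the trial with the fewest patients and the shortest follow-up, while the cited recurrences come late. The count is not related to how many patients have received the device or for how long they have been observed. When the window closes, most patients are still to be randomised, and as written nothing can then bring the committee together. The word *only* also rules out a meeting for other serious device-related events.

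At stake is whether the one independent continuation review would take place if device patients did clearly worse than standard of care. The primary cost-utility estimate is not affected.

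**Working it through.** **The plan's own figure.** The article gives no operating characteristics for the trigger, but its sample size can be checked ("considering alpha-risk at 0.05, power of 80% in a bilateral situation and approximately 10% of early withdrawal"). For 20% against 6%, mean 13%, pooled formula:

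n = [1.96·√(2·0.13·0.87) + 0.842·√(0.20·0.80 + 0.06·0.94)]² / 0.14² = (0.932 + 0.392)² / 0.0196 ≈ 89.4, so 90 per arm. Then 90/0.9 = 100 per arm. The 100 device patients used below are confirmed.

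**Exposure in year 1.** Even accrual is an assumption.

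- Device patients entering in year 1: 100 × 12/36 ≈ 33. About 67 enter later.
- Follow-up by month 12 with lag L months to surgery: (100/36)·(12 − L)²/2 patient-months. This is 200, 168 and 139 for L = 0, 1 and 2.
- The arm's planned total is 100 × 24 = 2,400 patient-months, so the shares are 8.3%, 7.0% and 5.8%.

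**Chance that the trigger fires (at least 4 recurrences).** For a true 24-month rate p, the constant monthly hazard is h = −ln(1 − p)/24. Expected year-1 events are

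E = (100/36)·[(12 − L) − (1 − e^(−h(12 − L)))/h].

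Example, p = 0.40 and L = 0: h = 0.02128 and (1 − e^(−0.2554))/h = 10.59, so E = 2.778 × 1.41 = 3.92. The Poisson chance of at least 4 is 1 − e^(−3.92)(1 + 3.92 + 7.68 + 10.04) = 0.55.

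The last column instead spreads recurrences evenly over days 145 to 563 and uses a binomial with 33 patients. Entries are for a lag of 0 / 1 / 2 months.

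| True 24-month rate | Expected year-1 events, constant hazard | Chance of meeting, constant hazard | Chance of meeting, days 145–563 |
|---|---|---|---|
| 6% (planned device rate) | 0.51 / 0.43 / 0.36 | 0.2% / 0.1% / <0.1% | all <0.1% |
| 20% (no benefit) | 1.79 / 1.51 / 1.25 | 11% / 7% / 4% | 2% / 0.7% / 0.2% |
| 40% (twice standard of care; assumed harm scenario) | 3.92 / 3.31 / 2.76 | 55% / 42% / 30% | 16% / 7% / 2% |

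A binomial with 33 patients in place of the Poisson gives 9.9% and 55% at 20% and 40% without lag. Under constant hazard, an even chance of firing needs a true 24-month rate of about 38%, 44% or 50% for a lag of 0, 1 or 2 months.

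**Sensitivity to early timing.** If every recurrence fell evenly within 12 months of surgery, the chance at 40% would be 92% / 83% / 69%. That implies a mean delay of about 6 months, which fits poorly with the cited 11.2 months and 145 to 563 days.

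**Why the same count cannot simply be extended.** Over the whole trial, 6% of 100 gives 6 expected events. The Poisson chance of at least 4 is then 1 − e^(−6)(1 + 6 + 18 + 36) = 0.85. A fixed count of more than three would therefore usually be reached when the device performs exactly as planned.

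**The case against.** Several points on the other side stand.

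- **The trigger is not close to useless.** A reader might infer that the committee has almost no chance of meeting in a harmful scenario. The figures do not support that: at 40%, constant hazard gives 55% without lag and 42% with a 1-month lag.
- **No benefit is not harm.** A low chance of meeting at 20% is not in itself a failure, because the device then only matches the planned control rate. A rate of 12%, double the planned device rate, is still below control.
- **The 145-day timing is fragile.** It rests on four events in one series. It shows when those four occurred, not that earlier recurrence is impossible, and Table 1 records recurrence from the day of surgery. It serves here as a sensitivity case only.
- **Other oversight exists.** Adverse events are recorded from inclusion, serious ones go to the sponsor, and device incidents go to the sponsor and the French agency (2.9). A blinded committee reviews recurrences, and the Scientific Committee is regularly informed. It would be wrong to infer that device events go unreviewed. None of these routes, however, is described as able to convene the Independent Safety Committee.
- **Device-related events should be named as the plan names them.** Section 2.6.1 gives hypercalcaemia, prolonged serous discharge, heterotopic ossification and allergy as examples. Acute renal failure is a separate outcome and fracture sits under complications, so neither should be presented as listed device harm.
- **The article is condensed.** The full protocol or a charter may contain further review rules. But the article states a rule rather than omitting one, and *only* leaves no room for a second trigger as written.

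**Conclusion.** The concern holds in a measured form. The rule gives at best about an even chance of convening the committee if device-arm recurrence is twice the standard-of-care rate. That chance falls to about 42% or 30% with a realistic lag to surgery, and to 16% or less if recurrences follow the cited 145-to-563-day timing. After month 12 the trigger has no force, although about two thirds of patients are still to be randomised and more than 90% of the device arm's follow-up is still to come.

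The figures assume even accrual of 100 device patients over 36 months and, in the main case, a constant hazard; the 40% rate is an assumed harm scenario. A slow start to recruitment would lower the chances, and markedly earlier recurrence would raise them. They also take the first year of the study literally. If each patient's first year was meant, across all 100 device patients, the rule would behave very differently: about 36% at 6% (12-month risk about 3.05%) and over 99% at 20%. The text does not say that.

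**What to change.** Amend section 2.1 and the committee's charter:

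1. Keep the convening trigger active through all enrolment and follow-up.
2. Express it relative to the number of patients implanted and their accumulated follow-up, not as a fixed count.
3. State its operating characteristics at the plan's own 6% and 20% and at a rate regarded as harmful.
4. Remove *only*, so that the committee can also be convened for serious device-related events.
5. If each patient's first year was intended, correct the wording to say so.

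Numerical thresholds are for the committee and the sponsor to set. The cost is protocol and charter wording plus a short calculation. The downside is possibly additional meetings of a committee that already exists.
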